#### Interim analyses {21b}

No interim analyses are planned.

### Methods for additional analyses (e.g., subgroup analyses) {20b}

#### Subgroup analyses

We will test for possible subgroup factors such as being partnered and currently trying to conceive. These are known moderators for HRQoL reductions through endometriosis. As our sample is expected to be quite homogenous in age and gender, other subgroup analyses might not be functional.

#### Process evaluation

To evaluate the development of iCBT for patients with endometriosis, the weekly measures of endometriosis-related QoL and qualitative feedback are taken into account. We hope to identify helpful aspects and key mechanisms in improving HRQoL to further improve the intervention. No systematic qualitative approach in assessing participant feedback will be implemented.

### Methods in analysis to handle protocol non-adherence and any statistical methods to handle missing data {20c}

Data will be analyzed following the ITT principle. Missing data will be explored. Imputation of missing values is not intended, although multiple imputations might be used within sensitivity analyses assuming data are missing at random.

### Plans to give access to the full protocol, participant level-data, and statistical code {31c}

There is no additional protocol to this version. Because gynecological diseases still carry some stigma, we will decide on whether to publish participant-level data anonymously after trial completion. Psychological treatment of endometriosis is not yet common, so participants might easily be identified through some of the collected data. Only if we reach a sample size large enough to rule out identification of participants by some of their data (*N* ≥ 80) will we proceed to provide access to participant-level data without any kind of demographic information. Any other data, statistical code, or documentation may be provided by the corresponding author at request.

### Oversight and monitoring

#### Composition of the coordinating center and trial steering committee {5d}

The immediate trial team responsible for trial management, day-to-day support, and administration of the intervention will meet weekly. The wider team—including medical experts—will meet every 3 months. Due to the small size of our trial and the few researchers being involved, other committees such as a Trial Steering Committee or Project Management Group will not be formed.

#### Composition of the data monitoring committee, its role and reporting structure {21a}

Given the small size of our monocentric trial with few researchers involved and without external funding, there is no need for an additional data monitoring committee.

#### Adverse event reporting and harms {22}

Adverse events (AEs) will be collected and monitored by the therapists running the intervention. Any disadvantageous event occurring during the trial (e.g., worsening of symptoms, acute suicidal ideation, hospitalization due to mood deterioration) will be classified as an adverse event. Both AEs that are assumed to be a consequence of treatment and those that are not causally related to the treatment will be collected. All AEs will be discussed weekly regarding causality and severity, and possible further actions will be considered.

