### Interventions

#### Explanation for the choice of comparators {6b}

The comparator is a waitlist control. Patients in the waitlist control group can continue with their usual treatment plan during trial participation (e.g., medication or physiotherapy). Because there is, as yet, no established treatment as usual (TAU) for patients with endometriosis, using a waitlist control seemed reasonable to capture real-life conditions. Patients currently receiving psychotherapy or seeking psychotherapeutic treatment in the past 2 years will be excluded from trial participation.

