Participants are asked to spend 1 to 2 h on each module. After each week, participants receive written feedback from a trained psychologist based on their input into the treatment platform. The participants can ask questions regarding the module they have been working on via text messages to their psychologist on the online platform. The psychologist is at least a bachelor-level clinical psychologist and receives regular supervision by a licensed CBT therapist.

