#### Negative effects of treatment

To detect possible negative effects of treatment in this trial (e.g., increased stress, new symptoms, hopelessness, and dependency), the Negative Effect Questionnaire (NEQ) [68] will be implemented.

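### Adverse event collection is assigned to the iCBT therapists and no route is described for the waitlist arm, so recorded event counts would not be comparable between arms

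*Protocol article*

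**What the plan says.** Section {22} names one collector: "Adverse events (AEs) will be collected and monitored by the therapists running the intervention". Its definition of an adverse event is broad (the quote stops one word short of the full sentence): "Any disadvantageous event occurring during the trial (e.g., worsening of symptoms, acute suicidal ideation, hospitalization due to mood deterioration) will be classified as an adverse". It is not limited to suspected treatment effects: "Both AEs that are assumed to be a consequence of treatment and those that are not causally related to the treatment will be collected". Collected events then go to case review: "All AEs will be discussed weekly regarding causality and severity, and possible further actions will be considered".

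The intervention description {11a} shows how the therapists learn about iCBT participants: "After each week, participants receive written feedback from a trained psychologist based on their input into the treatment platform". Participants can also send them text messages on the platform, and the adherence section {11c} again relies on weekly contact. For the waitlist arm, the comparator section {6b} says only that usual care may continue.

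A second harms instrument appears under process evaluation. Its purpose is given as "To detect possible negative effects of treatment in this trial", and the article says for this that "the Negative Effect Questionnaire (NEQ) [68] will be implemented". It is scheduled post-treatment and at follow-up, with no arm named.

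The efficacy scales are collected differently. Under {12} and {18a}, both arms complete the same online self-report measures at baseline, post-treatment and 3 months. Only the iCBT arm continues to 12 months.

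**The concern.** The definition covers both arms, but the stated means of detection reaches only one. Events such as worsening symptoms, suicidal ideation or hospitalisation also occur in people with endometriosis who receive no trial treatment, so a count under iCBT means little without a control rate obtained in the same way. If one arm is in contact with the collectors every week for eight weeks and the other has no described contact, the two counts measure detection as well as risk.

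There are two consequences. If counts are shown side by side, iCBT may look harmful when it is not, or a true excess may be dismissed as an artefact of closer observation. Acute events on the waitlist could also go unrecorded. Nothing else described would reveal the imbalance: there is no blinding ({17a}), no data monitoring committee ({21a}) and no independent audit ({23}). The efficacy conclusions are not affected.

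**Working it through.** The article gives no figure on adverse events, so there is nothing to reproduce. The check compares the provisions by arm and then illustrates the size under stated assumptions.

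**Step 1: routes by which a harm could be recorded**

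| Route | iCBT arm | Waitlist arm |
|---|---|---|
| Therapist collection ({22}, {11a}, {11c}) | Weekly contact | None described |
| NEQ (process evaluation) | Post-treatment and follow-up | Not stated; items concern treatment effects |
| EHP-30+23, pain, PDI, PHQ-9, PSS-10 ({12}, {18a}) | Baseline, post-treatment, 3 and 12 months | Baseline, post-treatment, 3 months |

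Only the last row is symmetric, and only to 3 months. It can show worsening scores. It is not described as an adverse event route and would not record a hospitalisation.

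**Step 2: could the route be set out elsewhere?** Section {31c} says that no other protocol exists. Who collects events, and from whom, is trial conduct and not a detail normally left to an analysis plan. The participant timeline (Fig. 1) could not be read, so this step rests on the text.

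**Step 3: illustration**

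Inputs from the article: 120 participants ({14}) at 1:1 ({8}), so 120 / 2 = 60 per arm.

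Assumed, not in the article: the same true risk p in both arms (10%, 20% or 30%), 90% of events detected under iCBT, and 0%, 25% or 50% on the waitlist.

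Recorded events = 60 × p × detection rate. For p = 20%:
- True events: 60 × 0.20 = 12 per arm
- iCBT: 12 × 0.90 = 10.8
- Waitlist: 12 × 0 = 0; 12 × 0.25 = 3.0; 12 × 0.50 = 6.0

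Spurious risk difference Δ = p × (0.90 − waitlist detection rate).

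The chance of a false significant difference (two-sided 5%, normal approximation) is Φ[(Δ − 1.96 × SE0) / SE1]. Here SE0 = √(2 × p̄ × (1 − p̄) / 60), with p̄ the mean of the two recorded proportions, and SE1 = √((p1(1 − p1) + p0(1 − p0)) / 60). For 18% against 10%: SE0 = 0.0634, SE1 = 0.0629, (0.08 − 0.1242) / 0.0629 = −0.70, giving 24.1%.

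| True risk | iCBT recorded | Waitlist recorded at 0 / 25 / 50% detection | Difference, points | Chance of false significance |
|---|---|---|---|---|
| 10% | 5.4 | 0 / 1.5 / 3.0 | 9 / 6.5 / 4 | 66.6 / 33.2 / 13.5% |
| 20% | 10.8 | 0 / 3.0 / 6.0 | 18 / 13 / 8 | 94.1 / 60.9 / 24.1% |
| 30% | 16.2 | 0 / 4.5 / 9.0 | 27 / 19.5 / 12 | 99.5 / 81.5 / 36.3% |

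The approximation is rough at such small counts. With equal detection the expected difference is zero. The ratio of expected counts is just the ratio of the two assumed detection rates (0.90 / 0.50 = 1.8; 0.90 / 0.25 = 3.6), so no single risk ratio should be read as an estimate.

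**The case against.** The strongest reply is that {22} does not restrict collection to the iCBT arm. Its definition covers the whole trial, and naming the therapists does not bar a report from a waitlist participant. Section {5d} describes one small team that runs the trial, supports it day to day and delivers the intervention, so waitlist reports might reach the same people. This stands in part. A reader might infer that therapists are the sole source and that waitlist events are excluded, but the text does not say so; the route is undescribed, not ruled out. Equally, the team structure does not show that a route exists.

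Second, a reader might infer that harms cannot be compared at all. That is too strong. Symptom worsening is the first example in {22} of an adverse event, and the scales that capture it are administered identically in both arms to 3 months. What cannot be compared is the recorded event count.

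Third, harms are not a listed outcome, and {20a} plans no between-arm test of adverse events; {22} describes case review. This also stands. The false-significance figures therefore show how far counts could mislead if set side by side, not the error rate of a planned analysis.

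Fourth, weekly written feedback is not the same as weekly questioning about events, so high detection under iCBT is an assumption. That is why a range is shown. The direction holds whenever detection is better under iCBT.

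**Conclusion.** The point holds in this form: event collection is assigned to staff in weekly contact with one arm, and no route is described for the other, although the definition covers both. Recorded adverse event counts would be subject to differential ascertainment and could not be validly compared between arms, and acute waitlist events could be missed. The documents do not support saying that waitlist events are excluded or that no harms comparison is possible: deterioration on the EHP-30+23, pain, PDI, PHQ-9 and PSS-10 can be compared to 3 months.

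The size is illustrative. At 20% true risk, 60 per arm and 90% detection under iCBT, 10.8 recorded events stand against 0 to 6.0 for waitlist detection of 0% to 50%, a spurious difference of 18 to 8 percentage points. The detection rates and the true risk are assumptions. The point is worth correcting because missed events are hard to reconstruct later, but it leaves the primary efficacy analysis untouched.

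**What to change.** - Add one short, identical event list (symptom worsening, suicidal ideation, hospitalisation, other) to the existing online questionnaires at post-treatment and 3 months in both arms.
- State in {22} that any between-arm statement about adverse events rests on that list, and that events detected by therapists are tabulated separately as iCBT-arm data.
- Report by arm, to 3 months, the proportion who deteriorate on scales that both arms already complete, such as the PHQ-9, with the definition of deterioration fixed in advance.
- State whether the waitlist arm receives the NEQ.

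The cost is a few items in a battery that both arms already complete and a few sentences of text. The drawbacks are slightly more questionnaire burden and the need for the team to review the event answers; how they act on them is for the investigators to set. Two retrospective assessments make the counts comparable, but they do not give the waitlist the week-by-week detection that the iCBT arm has.

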**Methods:**

This is a monocentric randomized-controlled trial recruiting 120 patients with endometriosis. The intervention consists of eight iCBT modules focusing on psychoeducation, cognitive restructuring, pacing, and emotion regulation. Participants will receive written feedback from a trained therapist weekly. The comparator is a waitlist control group. All participants will be followed up 3 months after the intervention, and the intervention group will additionally be followed up 12 months after the intervention. Trial participants will not be blinded to the allocated trial arm. Primary outcome measures are endometriosis-related QoL, pain, and pain-related disability. Secondary outcomes include coping, illness representations, and psychological flexibility. Statistical analyses will be performed following intention-to-treat principles.

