#### Plans to promote participant retention and complete follow-up {18b}

Participants will be contacted for follow-up via e-mail. The data are collected online, reducing as many barriers as possible (e.g., having to schedule an in-person appointment or sending the questionnaires back). There is no additional incentive for participants to complete the trial. Based on our experience working with patients who suffer from endometriosis, the sample is usually grateful for any research conducted on endometriosis and tends to be very eager to participate.

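### Adverse events of any cause are to be collected only by the iCBT therapists, with no route described for the waitlist, so the therapist-recorded AEs cannot show whether harms exceed the waitlist background

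*Protocol article*

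**What the plan says.** Section {22} of the protocol article makes three statements that matter here.

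- Who collects: "Adverse events (AEs) will be collected and monitored by the therapists running the intervention". No other collector is named.
- What counts: "Any disadvantageous event occurring during the trial (e.g., worsening of symptoms, acute suicidal ideation, hospitalization due to mood deterioration", with the list in the sentence serving as examples. There is no end date and no restriction to one arm.
- Which causes: "Both AEs that are assumed to be a consequence of treatment and those that are not causally related to the treatment will be collected".

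Therapist contact is described under the intervention. Section {11a} says "After each week, participants receive written feedback from a trained psychologist based on their input into the treatment platform", and adds text messaging about the current module. Section {11c} relies on weekly psychologist contact to support adherence. For the comparator, section {6b} says "Patients in the waitlist control group can continue with their usual treatment plan during trial participation". Section {18b} says "Participants will be contacted for follow-up via e-mail". Neither mentions adverse events.

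Both arms are assessed at baseline, post-treatment and 3 months. Beyond that, according to the abstract, "the intervention group will additionally be followed up 12 months after the intervention". The Negative Effect Questionnaire (NEQ) is also planned, with the purpose "To detect possible negative effects of treatment in this trial". The text does not say whether the waitlist completes it.

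**The concern.** The definition and the means of collection do not match. The definition covers everything that goes wrong for any participant, whereas the only named collectors are the people who deliver one arm's treatment. A participant who writes to a therapist every week has an obvious occasion to report worsening. A waitlisted participant has no described occasion.

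This matters because the first example of harm in section {22}, symptom worsening, also happens in untreated endometriosis. Whether iCBT makes some participants worse can be judged only against the waitlist. If therapist-recorded events were later shown by arm, a difference in contact could be read as a difference in risk, most likely to the disadvantage of iCBT.

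The planned efficacy analyses do not fill the gap. Section {20a} describes a repeated-measures comparison of means and covariance models. An average improvement can coexist with a minority who deteriorate.

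**Working it through.** The plan states no AE figure, so there is none to reproduce. The check is a comparison of sections, followed by three short calculations.

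**1. Definition against collection**

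| Feature | iCBT arm | Waitlist |
|---|---|---|
| Covered by the AE definition ({22}) | yes | yes |
| Therapist contact described ({11a}, {11c}) | weekly, during 8 modules | none |
| Other AE route described | none | none |
| Online self-report scales to 3 months ({12}, {18a}) | yes | yes |
| NEQ (Process evaluation in {12}) | post-treatment and follow-up | arm not stated |

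The NEQ is aimed at effects of treatment, so it does not replace any-cause AE collection, least of all in people not yet treated. The PHQ-9, EHP-30 core, pain scales and PDI are collected alike in both arms, but no section makes them a source of AEs.

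**2. Described contact within the common period**

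Inputs: 8 weeks of intervention ({8}, {11a}) and 3 further months, taken as 13 weeks.

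- Common period: 8 + 13 = 21 weeks per participant.
- Described therapist contact, iCBT: 8/21 = 38% of that time.
- Described therapist contact, waitlist: 0/21 = 0%.

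This is contact as described, not measured AE coverage.

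**3. What unequal capture would do**

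Assume equal true AE rates in both arms over the common period, and let *s* be waitlist capture as a fraction of iCBT capture. The recorded ratio, iCBT to waitlist, is then 1/*s*.

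| *s* (assumed) | Recorded ratio |
|---|---|
| 1.00 | 1.0 |
| 0.75 | 1.33 |
| 0.50 | 2.0 |
| 0.25 | 4.0 |

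The document gives no value for *s*. The table shows the direction and how strongly the result depends on *s*; it is not an estimate. Adjusting for person-time would not remove this ratio, because it comes from contact and not from length of observation.

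**4. Precision of a by-arm worsening table**

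Half-width of the 95% interval for a risk difference: 1.96 × √[(p₁(1−p₁) + p₂(1−p₂))/n], with n per arm. Section {14} plans 120 participants and section {8} allocates 1:1, so n = 60. The worsening proportions and the losses are assumptions.

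| n per arm | 15% in both arms | 10% vs 20% |
|---|---|---|
| 60 (no loss) | ±12.8 points | ±12.7 points |
| 48 (20% lost) | ±14.3 points | ±14.1 points |
| 42 (30% lost) | ±15.3 points | ±15.1 points |

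Example: 1.96 × √(2 × 0.15 × 0.85/60) = 1.96 × 0.0652 = 0.128.

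**The case against.** The strongest reply is that nothing planned is wrong. The protocol promises no by-arm AE comparison and no AE test. Tabulation rules, windows and cut-offs normally belong in an analysis plan, and section {20a} refers to one. That stands for the table details. It does not cover who collects AEs and from whom, which is protocol content, and section {31c} says that no further protocol exists.

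A second reply is that unequal capture is inferred. This also stands. A reader might conclude that waitlist AEs go unrecorded, but the documents do not say so. Section {22} sets no arm limit, the small team delivering the intervention also handles trial management and day-to-day support ({5d}), and the participant timeline figure is not shown.

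A third reply concerns waitlist access. The Limitations section declines to withhold a potentially effective treatment from controls, which implies that they receive iCBT, and hence therapist contact, later on. The text shown gives no date and does not say whether AEs are recorded then. This makes whole-trial counts harder to interpret as treated against untreated. It is a reason to confine any comparison to the common period.

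Two stronger quantitative readings are tempting. Follow-up of 8 + 52 = 60 weeks against 21 weeks might suggest about 2.9 times as many iCBT events at equal rates. That needs equal capture in both arms throughout follow-up, which conflicts with the argument that capture follows contact, and it needs raw counts over unequal windows, which the plan does not propose. One could also assume 15% worsening with 80% against 20% captured and obtain a false excess of 0.15 × 0.60 = 9 points, but every input to that figure is assumed.

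**Conclusion.** The point holds as a limit on what the harms data can show. As written, the plan would probably record AEs more completely under iCBT than on the waitlist, and therapist-recorded AEs cannot establish whether worsening exceeds the untreated background. This rests on two things: the only named collectors are the iCBT therapists, and the only therapist contact described is in the modules. It also assumes that reporting follows contact, which the documents neither confirm nor rule out.

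No size can be given for the resulting bias. It is zero if capture is equal over the common period and grows as waitlist capture falls. The efficacy analysis is not touched. Severity is minor to moderate, and the case for acting rests mainly on how cheap the remedy is.

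**What to change.** 1. In sections {22} and {18a}, add one identically worded AE question to the online questionnaires that both arms already complete at post-treatment and 3 months. Limit any between-arm AE summary to that common period, before any later waitlist access to iCBT.
2. Report descriptively, by arm and at the same two times, the number and percentage worsened from baseline on scales already collected, for example PHQ-9, EHP-30 core, pain scales and PDI. Give the risk difference, its 95% interval and the number missing. Set the cut-offs in the analysis plan before data lock.
3. State that therapist-recorded AEs and the 12-month data are uncontrolled information on the iCBT arm.

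The cost is one extra question, one descriptive table and a few lines of text, with no new visit or staff. Version 1 is dated before the planned start of recruitment. The limits remain: both sources depend on self-report by those who complete the questionnaires, and the intervals are too wide for the table to serve as a test. Without step 1, events that no scale measures, such as hospitalization, would stay unevenly captured.

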#### Plans for communicating important protocol amendments to relevant parties (e.g. trial participants, ethical committees) {25}

The local ethic committee will be notified for approval if any protocol modifications are required. Trial registries and the trial protocol would be updated.

